## Abstract

**Background and purpose:**

In the Netherlands, care for head and neck cancer (HNC) is centralised in head and neck oncology centres (HNOCs). Follow-up after treatment requires frequent visits that can burden patients and providers. Telemedicine, through remote evaluation of laryngopharyngoscopy videos recorded at local hospitals, may offer a feasible alternative. This study protocol describes the aim to assess patient satisfaction and safety with telemedicine follow-up after treatment of (pre-)malignant glottic lesions, including severe dysplasia, carcinoma-in-situ and T1 squamous cell carcinoma, conducted at one HNOC and participating general hospitals.

**Methods and analysis:**

As a non-blinded, randomised controlled trial, 90 patients with a one-way travel time by car of over 45 min to the HNOC will be allocated to the intervention group (follow-up by an Ear, Nose and Throat surgeon at a nearby participating hospital) or the control group (standard follow-up at the HNOC). All patients undergo guideline-based care. In the intervention group, laryngopharyngoscopy recordings will be remotely reviewed by HNOC specialists on the same day. Surveys will be fulfilled at baseline, 6 and 12 months. The primary outcome is overall patient satisfaction using a 0–10 numeric rating scale at 12 months follow-up. Secondary outcomes are safety, quality of life, fear of recurrence, travel time and carbon-dioxide emission. Safety will be assessed through recurrence, complications, re-referral and survival. Between-group and within-group comparisons will be performed to evaluate differences in outcomes, using appropriate statistical methods based on data distribution.

**Ethics and dissemination:**

This study explores regional collaboration and sustainable follow-up for HNC patients. The ethics board approved the protocol (M23.325004). The authors commit to publishing the findings.

**Trial registration number:**

ClinicalTrials.gov ID NCT06940505.

## Introduction

Globally, head and neck cancer (HNC) is the 7th most common cancer diagnosis [1]. The most common primary sites include carcinomas of the oral cavity, pharynx and larynx. In recent years, the overall incidence of HNC in the Netherlands has increased, mainly due to the rise in human papilloma virus-related squamous cell carcinoma of the oropharynx [2, 3].

Aiming to detect cancer without delay and identify recurrences early, patients follow a rigorous post-treatment schedule. In the Netherlands, follow-up for HNC patients is centralised in head and neck oncology centres (HNOCs) [4]. Dutch guidelines advise visits every 2 to 3 months during the first 2 years, and every 4 to 6 months in the following 3 years [4]. This applies to all HNC patients, despite significant differences in recurrence rates and prognosis [2]. Centralised care requires some patients to travel long distances, creating financial and practical burdens for them and their caregivers [5, 6]. With a growing patient population, head and neck oncologists also face challenges in maintaining oncologic (follow-up) care. There are several efforts to address rising costs and burden, advocating for digital innovations, regional cooperation and sustainable solutions [7].

The need to revise the patient-care pathway is also internationally recognised and extends beyond HNC to other oncological fields [8–12]. One proposed solution is patient-initiated follow-up, where patients schedule consultations based on symptoms, abandoning a generalised schedule [8, 13]. However, this may be less sustainable for older or frail patients. Evidence that routine follow-up for (head and neck) cancer improves clinical outcomes is generally lacking [14, 15]. An exception may be early-stage glottic carcinoma after transoral laser surgery (TOLS), for which reported recurrence rates vary widely, ranging from 9 to 25% depending on the tumour stage and follow-up duration [16–19]. Early detection may allow limited revision surgery instead of escalating to multimodality treatment with radiotherapy [14, 15, 17, 20]. Patients also report that follow-up reduces fear of recurrence and provides psychosocial support [12]. Follow-up for HNC usually includes high definition (HD)-laryngoscopy, which has a high detection rate for malignancies, and adding narrow-band-imaging (NBI) improves detection even further [16, 21].

Building upon the idea of regional cooperation whilst making use of technological advancements, follow-up by an Ear, Nose and Throat (ENT) surgeon at a nearby hospital combined with remote evaluation of laryngoscopy videos (telemedicine) may offer a practical solution. Telemedicine follow-up addresses the burden of travel, which may also reduce carbon-dioxide (CO_2_) emissions [22].

Therefore, a study was primarily designed to assess patient satisfaction with telemedicine follow-up after TOLS for pre-malignant lesions and early-stage glottic carcinoma (severe dysplasia, carcinoma-in-situ and T1 squamous cell carcinoma), using patient-reported outcome measures (PROMs) and patient-reported experience measures (PREMs). To the best of our knowledge, no comparable previous studies have been performed before. PROMS and PREMs are widely used standardised tools to assess patients’ health status and experiences with care from their own perspective. PROMs assess health outcomes like symptom burden and quality of life, whilst PREMs focus on aspects such as communication, accessibility and overall satisfaction [23, 24]. Moreover, we aim to evaluate if both follow-up techniques are equally safe in terms of detection of disease recurrence, complications, re-referral and survival.

## Methods and analysis

### Study setting

This non-blinded, randomised controlled trial (RCT) is carried out at the Department of Otorhinolaryngology, Head and Neck Surgery of the University Medical Center Groningen (UMCG), a HNOC and academic tertiary referral hospital in the Netherlands. The participating general hospitals are Isala Medical Centre and Saxenburgh hospital. The Dutch HNC patient association (Patiëntenvereniging Hoofd-Hals, PVHH) provided valuable input into the development of the study design. This protocol is reported according to the SPIRIT guideline (Supplementary information A) [25].

### Eligibility criteria

Inclusion criteria include patients who underwent TOLS for severe dysplasia, carcinoma-in-situ or T1 squamous cell carcinoma, have a one-way travel time (by car) to the HNOC of > 45 min and have the possibility of follow-up in a nearby participating hospital. In addition, patients are eligible for inclusion if they are within 2 years postoperatively and can speak and write Dutch (Figure 1). Patients will be excluded if they continue to undergo follow-up for other cancers in the HNOC. Written informed consent will be obtained from all patients (Supplementary information B).

**Figure 1 F0001:**
[figure not shown]
Inclusion and follow-up protocol. TOLS: transoral laser surgery; TCIS: carcinoma in-situ; HNOC: head and neck oncology centre; PROM: patient-reported outcome measure; PREM: patient-reported experience measure.

### Interventions

Figure 1 visualises the study flow. Included patients will be randomly assigned to one of two groups: an intervention group and a control group. Follow-up is performed though standardised follow-up guidelines and is equal for all patients, with at least of 4 to 6 consultations expected [4]. The control group will receive their oncological follow-up in the UMCG. The intervention group will receive their oncological follow-up by an ENT surgeon in a hospital that is closer to the patients’ home. A reduction in travel time of more than one-third was considered indicative of closer proximity to home, as it is believed that it would be a significant time reduction for the patients. A history will be taken, and a complete ENT physical examination will be performed, including flexible HD-video laryngopharyngoscopy (with or without NBI) and neck palpation. HD-laryngopharyngoscopy is performed with digital transnasal flexible endoscopes of XION (XION GmbH, Berlin, Germany) or Olympus (Olympus Nederland BV). The videos obtained during the follow-up visit will be digitally transferred and securely stored in the electronic patient files in the HNOC, for the same day assessment by a head and neck oncologist. Furthermore, the head and neck oncologist has access to the patients’ previous examinations, (surgical) history and findings or concerns of the ENT surgeon who has seen the patient earlier that day. After evaluation, the patient is contacted by the HNOC to share the results, and a new management plan (such as re-referral to the HNOC) is formulated if necessary.

Patients who do not wish to participate in this randomised controlled study will be asked to complete the questionnaires that are part of this study whilst receiving their follow-up in HNOC (the ‘preference group’).

### Outcomes

Our primary outcome is satisfaction with care and is measured on a 0–10 numeric rating scale (NRS) at 12 months post-inclusion. Our secondary outcome is safety, which is evaluated and measured by recurrence, re-referral rate, complications following recurrence treatment and survival. For the secondary outcomes, patients will be followed for at least 1 year after inclusion. Safety outcomes are only assessed after the study termination, thereby aiming for at least 2 years follow-up per patient. All outcome measures are outlined in Table 1.

**Table 1 T0001:** Outcome measures.

Outcome measure	Assessment	Evaluation method	Timing of evaluation

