### Statistical analysis

Descriptive statistics will be used to summarise patient’s baseline characteristics. Categorical variables will be presented as absolute numbers and percentages of the total. Continuous variables are tested for normality using Kolmogorov-Smirnov analysis and will be presented as means and SDs for normally distributed data, and medians and interquartile ranges for non-normally distributed data. Between-group mean (or median) differences, rate differences and rate ratios with 95% confidence intervals (or ranges) will be calculated. The groups will be compared using the Wilcoxon signed rank test or the Mann-Whitney test for non-normally distributed data, the independent t-test for normally distributed data and chi-squared test for categorical variables. Additionally, within-group changes will be assessed with paired t-tests (continuous data) and the McNemar test (categorical data). Kaplan-Meier survival analysis will be performed for disease-specific and overall survival. The EQ-5D-5L, EORTC QLQ-H&N-35 and cancer worry scale (CWS) questionnaires will be analysed according to their manual [30–32, 34]. Total CO_2_ emission caused by travel to the hospital will be estimated and compared between groups based on the values provided by the European Environment Agency for the period 2010–2023 (130.1 g of CO_2_ per kilometre) [36]. Missing values will be handled using multiple imputation, assuming that there is only missingness at random, and all analyses will be performed on an intention-to-treat basis. The data will be reported according to the CONSORT guidelines [37].

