## Discussion and conclusion

This is the first prospective study investigating the novel concept of relocating follow-up care for HNC patients. Since the COVID-19 pandemic, telemedicine use has notably increased and is widely accepted by both oncologic and non-oncologic patients [26–28, 38]. In most telemedicine studies in otolaryngology, videoconferencing consultations are used, with remote physical examinations occasionally employed for otoscopic evaluations but not for laryngoscopic (follow-up) assessments [39, 40]. Advancements in HD-laryngoscopy and emerging Artificial Intelligence (AI) disease detection software may create opportunities to reorganise follow-up care for HNC patients, reducing dependency on physician expertise [41, 42].

The strength of the study is its RCT design and the inclusion of a preference arm. This study aligns with sustainability goals. The possibility of telemedicine follow-up offers a more flexible and patient-centred approach to care, reducing travel burden and increasing accessibility. It may also help alleviate pressure on specialised centres by enabling efficient, remote monitoring without compromising safety. A limitation of the study is the use of a non-validated survey. However, most questions are derived from validated questionnaires, and the benefit of validation of the survey was not seen. Additionally, patients in the intervention group will complete the survey in a different setting than those in the control group (i.e. at home with remote assistance through a telephone call and at the HNOC with assistance in person as needed), which may introduce bias. With the knowledge that a follow-up duration of 12 months is limited, safety outcomes will only be assessed after the conclusion of the study period. Furthermore, travel distances to hospitals in the Netherlands are typically shorter than in other countries; however, the findings of this study may also be applicable to larger countries, where they could potentially benefit an even greater number of patients. If patients are satisfied and safety is confirmed, future research should explore other patient groups suitable for telemedicine follow-up. Multicentre studies will be necessary to assess its national impact and inform guideline changes, benefiting patients, society and the environment.

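### Reading safety data after study end does not give late entrants the 2 years aimed for, and recurrence has no time-to-event analysis despite unequal follow-up

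*Protocol article*

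**What the plan says.** Under Outcomes, the article defines its secondary outcome: "Our secondary outcome is safety, which is evaluated and measured by recurrence, re-referral rate, complications following recurrence treatment and survival". It then sets a floor: "For the secondary outcomes, patients will be followed for at least 1 year after inclusion". The next sentence adds the longer aim for safety: "Safety outcomes are only assessed after the study termination, thereby aiming for at least 2 years follow-up per patient". Table 1 times every safety item at the end of follow-up without giving a date or duration. The Discussion returns to the matter without repeating the 2 years: "With the knowledge that a follow-up duration of 12 months is limited, safety outcomes will only be assessed after the conclusion of the study period".

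On analysis, the Statistical analysis section says: "Kaplan-Meier survival analysis will be performed for disease-specific and overall survival". No method is assigned to recurrence by name. The general provisions that would cover it are "Between-group mean (or median) differences, rate differences and rate ratios with 95% confidence intervals (or ranges) will be calculated" and "the independent t-test for normally distributed data and chi-squared test for categorical variables". Table 1 does collect the date on which a recurrence is diagnosed.

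On entry, the Eligibility criteria state that "patients are eligible for inclusion if they are within 2 years postoperatively".

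**The concern.** Two things do not fit together. First, the article presents late assessment as the means of reaching 2 years per patient. Opening the files after the study has ended changes when data are read, not how long the last entrants have been observed. The only firm floor is 1 year.

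Second, a minimum of 1 year combined with one reading at the end implies that early entrants are observed longer than late ones. A proportion with recurrence over such a mixture belongs to no time point. The Introduction itself says that published recurrence rates depend on follow-up duration.

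Recurrence is the safety event that the trial most needs to describe. The Introduction sets out to judge whether both forms of follow-up are equally safe in detecting it, and the Discussion makes further research in other patient groups conditional on safety being confirmed. A recurrence figure that cannot be read as a 1-year or 2-year risk serves that purpose poorly.

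**Working it through.** The article states no numerical target for safety, so there is no figure to reproduce. Its only sample-size calculation concerns satisfaction and is not used here.

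**Inputs from the article.** Floor of 1 year after inclusion; aim of 2 years (Outcomes). Entry up to 2 years after surgery (Eligibility criteria). Recurrence 9 to 25% (Introduction). 90 patients (Sample size).

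**Assumptions, because the article gives no value.** Uniform entry over A months; one reading of the files 12 months after the last inclusion; the 9 to 25% treated as cumulative over T = 2 or 5 years with constant hazard and counted from inclusion.

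**Step 1: who reaches 24 months from inclusion.** A patient entering at month t has A + 12 − t months at the cut-off. That is at least 24 if t ≤ A − 12, so the share is (A − 12)/A for A ≥ 12 and zero below.

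| A (months) | Follow-up at cut-off (months) | At least 24 months | Under 24 months |
|---|---|---|---|
| 12 | 12 to 24 | 0% | 100% |
| 18 | 12 to 30 | 33% | 67% |
| 24 | 12 to 36 | 50% | 50% |
| 36 | 12 to 48 | 67% | 33% |

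**Step 2: does counting from surgery help?** A patient included s years after surgery and followed for the guaranteed year has 1 + s years. Two years requires s ≥ 1. The criteria set only an upper limit on s, so a patient included soon after surgery still falls short.

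**Step 3: how much recurrence depends on length of follow-up.** With λ = −ln(1 − p)/T, the risk by time u is 1 − exp(−λu), and the expected number is 90 times that.

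| p | T (years) | Risk at 1 year | Risk at 2 years | Expected of 90, 1 year | Expected of 90, 2 years |
|---|---|---|---|---|---|
| 9% | 5 | 1.9% | 3.7% | 1.7 | 3.3 |
| 9% | 2 | 4.6% | 9.0% | 4.1 | 8.1 |
| 25% | 5 | 5.6% | 10.9% | 5.0 | 9.8 |
| 25% | 2 | 13.4% | 25.0% | 12.1 | 22.5 |

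The count roughly doubles from year 1 to year 2.

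**Step 4: what a crude proportion would show.** If follow-up is spread uniformly from 1 to b years, the expected crude proportion is 1 − (exp(−λ) − exp(−bλ))/((b − 1)λ). Take p = 25% and T = 2, so λ = 0.1438.

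- A = 12 months (b = 2): 1 − (0.8660 − 0.7500)/0.1438 = 19.3%.
- A = 36 months (b = 4): 1 − (0.8660 − 0.5625)/(3 × 0.1438) = 29.7%.

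The same hazard, with a 1-year risk of 13.4% and a 2-year risk of 25.0%, gives 19.3% or 29.7% according to recruitment time alone.

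**Step 5: what a better analysis can and cannot do.** By Schoenfeld's formula, a hazard ratio of 2 needs 66 events for 80% power at two-sided 0.05. With 3.3 to 22.5 events at 2 years, power is about 9 to 38%.

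**The case against.** A reader might infer that the two durations contradict each other. They need not. The second is worded as an aim, and the abstract lists other secondary outcomes (quality of life, fear of recurrence, travel time, emissions), so a 1-year floor for the whole set and a longer target for safety can coexist. What remains is an aim that the stated means do not deliver.

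The shares in Step 1 rest on an assumed cut-off. The article does not say that the study ends 12 months after the last inclusion, and a condensed article may leave that date to the full protocol. The shares show that late assessment does not by itself secure 2 years, not that the aim will be missed.

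The listed rate ratios could be person-time rates, which would allow for unequal follow-up. The article does not say so, and a person-time rate would still not be a risk at a stated time. Endpoint detail may also stand in an analysis plan that is not shown. However, the published text does choose a time-to-event method and restricts it to survival.

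Randomisation makes follow-up length similar in the two arms on average, so large systematic bias in the comparison is not to be expected. That point stands.

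Two further inferences are tempting but unsupported. One is that deaths and losses would count as recurrence-free: the article plans multiple imputation of missing values and does not describe such counting. The other is that survival will produce very few events: no mortality figure is given. Finally, the 9 to 25% relates to follow-up after treatment, while patients may enter up to 2 years later, so Steps 3 to 5 are illustrations and not forecasts.

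**Conclusion.** The point holds in limited form. The article guarantees 1 year after inclusion. Its aim of 2 years per patient does not follow from assessing safety after termination, and the text shown gives no origin or cut-off for those 2 years. Follow-up will therefore differ between patients, and the general comparisons to which recurrence is left give neither a 1-year nor a 2-year risk.

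Under uniform entry and a cut-off 12 months after the last inclusion, between one third of patients (36 months of recruitment) and all of them (12 months or less) would have under 24 months. The harm is lost interpretability of absolute recurrence risk and lost information, rather than marked bias between arms. Time-to-event analysis will not make the safety comparison well powered.

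**What to change.** **Analysis.** Extend the Statistical analysis section to time from randomisation to first recurrence, using the diagnosis dates already collected. Censor at last follow-up and treat death as a competing event. Report cumulative incidence by arm and the arm difference at 12 months with a 95% CI. The 1-year floor is meant to cover this time point for every patient.

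**Duration.** Choose one of two wordings in Outcomes:

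- Set the safety file cut-off at 24 months after the last randomisation and also report the 24-month difference by intention to treat. State whether the allocated setting continues to then. The article does not say, and its expected 4 to 6 consultations correspond to about 12 months at the guideline interval of 2 to 3 months (12/3 = 4, 12/2 = 6). If the setting does not continue, the 24-month difference includes time after the intervention.
- Or restate the guaranteed minimum as 1 year and drop the claim that late assessment leads to 2.

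**Cost.** The analysis change is wording and needs no new recurrence data. The later cut-off adds a later file extraction and delays the safety results by up to a year (24 − 12 months) after the satisfaction results. In either case the safety comparison stays low-powered and should be presented as estimation, with intervals rather than a claim of equal safety.

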**Patient satisfaction (PREMs)**			
Overall satisfaction with care	0–10 NRS	Survey	Baseline, at 6 and 12 months
**Satisfaction with travel time**	0–10 NRS	Survey	Baseline, at 6 and 12 months
**Specific satisfaction**	Questions about satisfaction with care from CQI questionnaires [33, 35]	Survey	Baseline, at 6 and 12 months
**Safety**			
Local and regional disease recurrence	In case of recurrence: date of diagnosis, clinical and pathological characteristics, date and type of treatment, time until treatment to assess for delay	Electronic patient file	End of follow-up period
**Complications post-recurrence treatment**	After treatment in case of recurrence: frequency of complications and type of complications	Electronic patient file	End of follow-up period
**Re-referral rate**	Frequency of re-referral of intervention group patients to HNOC	Electronic patient file	End of follow-up period
**Disease-specific and overall survival**	Overall mortality and mortality related to (recurrent) disease	Electronic patient file	End of follow-up period

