### Sample size and recruitment

A power analysis was performed to calculate the sample size needed to answer our primary research question. As telemedicine follow-up has not been studied in HNC patients, power analysis was based on data from non-oncologic populations [26–28]. Most of these studies are one-armed studies. These studies reported a mean patient satisfaction, measured with a NRS or VAS, of 8.6 to 8.8, with one study noting a baseline score of 8.2. Although these results may not be representative of the HNC population, we based our expectations with regard to the primary outcome on these studies, nonetheless. Patient satisfaction is estimated at 9 (standard deviation [SD] 1.8) in the intervention arm and 8 (SD 1.8) in the control arm. To detect a clinically relevant difference of 1 point with 80% power and a two-sided alpha of 0.05, at least 41 patients per group are required. With an expected drop-out of 10%, a total of 90 patients will be included. This analysis was performed using G*Power (version 3, Heinrich-Heine-Universität Düsseldorf, Germany). Patients are first informed about the study by their treating head and neck oncologist in the HNOC. If a patient meets the eligibility criteria, the researcher will provide additional information, and an informed consent will be obtained.

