### Allocation to study groups

An independent researcher will generate the randomisation chart to ensure allocation concealment for the patient, clinician and researcher. Randomisation will be performed in REDCap with a 1:1 allocation ratio. Block randomisation and stratification will not be used, as no baseline characteristics are expected to significantly influence the study outcomes. Blinding of the treatment allocation after randomisation is not feasible, as both patients and care providers will be aware of the hospital setting in which the follow-up takes place.

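### Complications are counted only after treatment of a recurrence, so the outcome draws on about 4 to 11 patients per arm and cannot show procedural harm from false alarms

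*Protocol article*

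**What the plan says.** The aim at the end of the Introduction is to evaluate whether the two follow-up routes are "equally safe in terms of detection of disease recurrence, complications, re-referral and survival". The Abstract is equally general: "Safety will be assessed through recurrence, complications, re-referral and survival". Neither limits which complications count.

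The Outcomes section defines safety as "recurrence, re-referral rate, complications following recurrence treatment and survival". The Safety block of Table 1 repeats the limit: "After treatment in case of recurrence: frequency of complications and type of complications". These data come from the electronic patient file at the end of follow-up. The Outcomes section also states that Table 1 sets out all outcome measures.

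Three other statements bear on the point:
- Table 1 defines re-referral for intervention-group patients only.
- Table 1 counts scheduled and extra visits, with no record of what was done at them or of any harm.
- Statistical analysis promises intention-to-treat for all analyses and offers rate differences and rate ratios, but gives no denominator for complication frequency.

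**The concern.** A follow-up route can cause harm in two ways. It can find a recurrence late, so that treatment is heavier. It can also raise a false alarm, so that a patient without recurrence undergoes a biopsy or repeat procedure. The outcome as defined can reflect only the first.

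The patients who can contribute are also selected after randomisation. To enter, a patient must have a recurrence that is detected and treated, and detection is what the two routes might alter. The Introduction says that early detection may permit limited revision surgery in place of multimodality treatment, so allocation could affect both who enters the subset and what treatment they receive. A route that missed recurrences during the observation period would produce fewer treated patients and, other things equal, fewer recorded complications.

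The Discussion makes extension to other patient groups depend on safety being confirmed. A finding of similar complication rates would rest on a handful of patients and leave one kind of harm unexamined.

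**Working it through.** **Plan's own figure.** The protocol gives no calculation for complications or for any safety outcome, so there is none to reproduce. The sample size is taken as stated; whether it follows from its own inputs is a separate matter.

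**Inputs.**
- Total size (Sample size and recruitment): "a total of 90 patients will be included".
- Evaluable size (same section): "at least 41 patients per group are required".
- Allocation (Allocation to study groups): "Randomisation will be performed in REDCap with a 1:1 allocation ratio". This gives 90 / 2 = 45 expected per arm. Blocking is not used, so the actual split may differ somewhat.
- Recurrence after laser surgery for early-stage glottic carcinoma (Introduction): "reported recurrence rates vary widely, ranging from 9 to 25% depending on the tumour stage and follow-up duration".

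**Patients who can contribute an event.** Expected number per arm = patients per arm × recurrence proportion.

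| Patients per arm | At 9% | At 25% |
|---|---|---|
| 45 (randomised) | 45 × 0.09 = 4.05 | 45 × 0.25 = 11.25 |
| 41 (after drop-out) | 41 × 0.09 = 3.69 | 41 × 0.25 = 10.25 |

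So about 4 to 11 per arm. This assumes that the quoted range applies over the trial's follow-up and that every recurrence is detected and treated. The true number may be lower: the range is for carcinoma, while Eligibility criteria also admit severe dysplasia and carcinoma-in-situ, and patients up to 2 years after surgery.

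**What a comparison within that subset could show.** With 4 against 4, the most extreme table (0/4 against 4/4) has a two-sided Fisher p-value of 2 / C(8,4) = 2 / 70 = 0.029. The next most extreme (0/4 against 3/4) has 2 × 4 / 56 = 0.14. Only complete separation would reach 0.05. The protocol gives no complication rates. If they are assumed to be 10% and 50%, the power of Fisher's test is 4% with 4 per arm, 12% with 5 and 36% with 11.

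**The two possible denominators.**
- *Treated recurrences.* The comparison is made in a subset formed after randomisation, which the follow-up route may affect. It is not protected by randomisation.
- *All randomised patients.* The arms stay comparable as randomised. Events can still come only from the same 4 to 11 patients per arm.

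**Where a complication of a benign work-up would appear.** Going through Table 1:
- Recurrence: no, its details are recorded only when there is a recurrence.
- Complications: no, by definition.
- Re-referral: shows that an intervention patient was sent back, not what followed, and has no control-arm counterpart.
- Survival: only if fatal.
- Visit frequency: may show an extra visit, not harm.
- Quality of life, symptom burden and cancer worry: surveyed at baseline, 6 and 12 months; they may reflect some burden but do not identify a complication.

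No row records it as an event.

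**The case against.** The strongest reply is that the restriction is deliberate and consistent. Outcomes and Table 1 agree, and the unqualified word in the Abstract and the aim can be read as shorthand. The main danger of remote follow-up is late detection, and complications of recurrence treatment are a reasonable downstream marker of it, beside the time to treatment that Table 1 also records. This stands as a reason to keep the measure. It does not make the measure sufficient for the broader aim.

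A reader might infer that intention-to-treat is lost for this outcome. The documents do not show that. Statistical analysis promises it for all analyses, and complications per randomised patient is a natural reading. The loss is conditional on treated recurrences being the denominator.

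A reader might also measure the gain from widening the definition by zero-event upper limits. From 1 − 0.025^(1/n), these are 60% for n = 4, 28% for n = 11 and 8% for n = 45. The arithmetic is right but the comparison is not: the first two bound risk per treated recurrence, the third risk per randomised patient. The third is already available under the current definition if all randomised patients are the denominator.

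Nor do the documents establish that remote readers over-call. The Interventions section gives the reader earlier examinations, the history and the local surgeon's findings. False alarms are a plausible harm, not a documented one. Part of their frequency can be derived in the intervention arm from re-referrals without recurrence, and extra visits are counted.

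Finally, a condensed article may leave general adverse-event recording to the full protocol. That is fair for recording procedures. But the article fixes the outcome definition and says that Table 1 holds all outcome measures, so the narrow definition is a stated rule and not an omitted detail.

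**Conclusion.** The concern holds as an under-measured safety outcome. Complications are limited to those after recurrence treatment, while the aim claims more. Events can come from about 4 to 11 patients per arm, on the assumptions of 45 per arm and the protocol's 9 to 25% range, and possibly from fewer. A complication of a work-up that proves benign is not captured as an outcome in either arm, whichever denominator is used. Whether the comparison also loses the protection of randomisation depends on a denominator that the article does not state.

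This is one component of a secondary outcome with no power calculation of its own. It weakens what can be said about equal safety and leaves the primary satisfaction analysis untouched.

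**What to change.** In the Outcomes section and in Table 1, define the outcome in both arms as complications after any invasive diagnostic or therapeutic procedure prompted by follow-up findings, whether or not a recurrence is confirmed. Count it per patient, with all randomised patients in each arm as the denominator. Report complications after recurrence treatment as a descriptive subset. Align the Abstract and the aim in the Introduction with this definition.

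The cost is wording and some extra abstraction, since the patient files are already reviewed at the end of follow-up. Events will remain sparse under the wider definition, so the result should be presented descriptively with its confidence interval and not as a demonstration of equal safety.
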